#### Planned Statistical Analysis

Data will be analysed using SPSS. Analysis will be preceded by data cleaning and assumption testing. A series of analyses are planned. The primary analyses will assess the efficacy of the ABCD Parenting Program in promoting improved parental wellbeing, parenting practices, parent-adolescent relationships and adolescent behaviour. Intervention efficacy will be assessed by comparing the outcomes of the wait-list control and intervention conditions post intervention and follow-up measures using a series of 2 × 2 mixed factorial Mancovas. Both completer and intention-to-treat analyses will be conducted. The between subjects factor will be condition (intervention, wait-list) and the within subjects factor will be time (post, follow-up). The maintenance of intervention effects will also be assessed by comparing pre, post and follow-up and long-term follow-up using repeated measures Manovas. Potential confounds (e.g., socioeconomic status) and moderators (e.g., child gender) will be explored.

Further analyses will include exploration of the predictors of intervention outcome, and a thorough analysis of treatment adherence, compliance with intervention and other process variables. Detailed descriptive analysis of pre-intervention adolescent, parent and family characteristics will also be conducted to thoroughly explore the characteristics of families attending an adolescent focused, universal parenting program. Secondary analysis will explore the relationships between parent, parenting and adolescents factors. Based on existing literature it is predicted that positive parenting practices and parental coping and wellbeing will be associated with positive adolescent outcomes. Structural equation modeling will be used to explore the direction and strength of these complex relationships.

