Parents that did not register for the program did not differ from those that did register in terms of their adolescent's age (*t*(353.9) = -1.23, *p *> .05) or sex (*χ*^2^(1) = .64, *p *> .05). Parents that registered for the program(*M *= 1039.6, *SD *= 68.1) had a higher Socioeconomic Indexes for Areas(SEIFA) Index of Relative Socio-economic Advantage and Disadvantage based on residential postcode(*t*(342.9) = 2.39, *p *= .017) than those who did not register for the program(*M *= 1021.5, *SD *= 74.6). This indicates that families of lower socioeconomic status were less likely to register for the program.

The 180 participants who returned consent forms and family demographic surveys were randomly allocated to intervention (n = 90) or wait-list control (n = 90) conditions. Of those allocated to the intervention condition 82 (91%) were successfully enrolled into a group. It was not possible to enrol 8 (9%) registered parents in the intervention condition into groups. Eight (10%) of the 82 enrolled in a group did not attend. Of the 90 parents allocated to the intervention condition 76 (84%) returned a completed pre-questionnaire. This included all 74 parents who attended a group and two parents who were enrolled in a group but did not attend. Sixty-eight (76%) of the 90 parents allocated to the wait-list condition returned a completed pre-questionnaire. This information is presented in Figure 1 below.

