## Strengths and Limitations

This study has been designed to address many of the limitations of previous research and to comply with the recommendations of the CONSORT statement [61,62]. The intervention was informed by theory and empirical research and directly targets the improvement of parenting skills, parental wellbeing and parent-adolescent relationships, factors known to protect against negative adolescent outcomes. Participating parents were randomly allocated to intervention or wait-list control conditions. A range of parent, parenting, adolescent and family outcomes were assessed using measures published in peer reviewed publications and validated for the present purpose. The long-term follow up for the intervention group is a particular strength of the present study. Follow-up at 6 month and 18 month intervals of the study will allow for the assessment of maintenance of change, and the efficacy of the program as an effective prevention strategy for promotion of factors known to protect adolescent from negative health and behavioural outcomes. The CONSORT tracking method [61,62] will also be used to allow for consideration of engagement processes and a thorough assessment of intervention attrition. This will also allow for both intention-to-treat and completer analyses.

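### The condition-by-time Mancova named for efficacy does not by itself deliver the promised intention-to-treat comparison

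*Protocol article*

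**What the plan says.** Planned Statistical Analysis fixes the software ("Data will be analysed using SPSS") and the efficacy model: intervention and wait-list are compared on "post intervention and follow-up measures using a series of 2 × 2 mixed factorial Mancovas". Condition is the between-subject factor. Time, with post and follow-up as its two levels, is the within-subject factor. The covariates are not named. The two analysis sets are promised directly after the model: "mixed factorial Mancovas. Both completer and intention-to-treat analyses will be conducted".

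Strengths and Limitations returns to the two analysis sets after describing CONSORT tracking of engagement and attrition: "This will also allow for both intention-to-treat and completer analyses".

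Statistical Power expects high dropout, more so on the wait-list, without giving a rate. Recruitment (under Results) shows how many forms were missing at the first wave: "Of the 90 parents allocated to the intervention condition 76 (84%) returned a completed pre-questionnaire", and "Sixty-eight (76%) of the 90 parents allocated to the wait-list condition returned a completed pre-questionnaire". It adds that the 76 were all 74 parents who attended a group plus two who were enrolled but did not attend.

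The article does not define the intention-to-treat set or the completer set. It does not say how parents without a post or 6-month form enter the model. Nor does it say that they will be left out.

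**The concern.** A repeated-measures Mancova works on complete rows. Without a further step, a parent contributes to a given Mancova only with every dependent scale in it at both waves and every covariate. Joining post and follow-up in one within-subject model therefore also discards parents who returned one of the two outcome forms, although their data are in hand.

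Two features of this trial make that matter. First, loss was expected to be heavy and unequal between arms. Second, the pre-questionnaire was collected after allocation: parents were randomised on receipt of the consent form and demographic survey, and intervention parents were then posted the pre forms two weeks before their scheduled group. Restricting to parents with a pre score is therefore a restriction made after randomisation, and in the intervention arm it follows attendance closely.

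At stake is whether the result carrying the intention-to-treat label compares the groups as randomised, or mainly compares attenders with those wait-list parents who kept returning forms.

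**Working it through.** **1. The article's own counts (Recruitment).** 76/90 = 84.4% and 68/90 = 75.6%, which reproduce the stated 84% and 76%. Non-attenders in the intervention arm: 8 not enrolled in a group + 8 enrolled but not attending = 16, and 90 − 16 = 74 attenders. Pre forms came from 74 attenders and 2 non-attenders, so all 14 intervention parents without a pre form (16 − 2) were non-attenders.

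**2. Ceiling if pre scores are covariates.** 76 + 68 = 144, and 144/180 = 80.0%. Already missing: 14/90 = 15.6% v 22/90 = 24.4%.

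**3. Make-up of the intervention arm.** Attenders among those who can enter: 74/76 = 97%. Attenders as randomised: 74/90 = 82%. The wait-list arm has no corresponding filter on attendance.

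**4. Room left against the article's target.** Recruiting 90 to secure 64 allows for a loss of 1 − 64/90 = 28.9%. Taking 64 per group at face value (whether it is right is a separate question), the pre form alone leaves 76 − 64 = 12 parents to spare in the intervention arm and 68 − 64 = 4 on the wait-list, before any later form is missed.

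**5. Later waves, illustration only.** The article gives no return rates. Assume a return rate r at each later wave, independent across waves, starting from 144.
- Both forms: 144 × r²
- At least one form: 144 × (1 − (1 − r)²)

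| r (assumed) | Both forms (unfilled Mancova) | At least one (mixed model) |
|---|---|---|
| 75% | 81 | 135 |
| 85% | 104 | 141 |
| 95% | 130 | 144 |

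Independence is the favourable case for the mixed model. With a within-parent return correlation ρ, the number with both forms is 144 × (r² + ρr(1 − r)), and the number with at least one falls by the same amount. At r = 75% and ρ = 0.5 that is 144 × (0.5625 + 0.09375) = 94.5 and 144 × (0.9375 − 0.09375) = 121.5. At ρ = 1 both are 108 and nothing is gained.

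**6. Simulated size, illustration only.** The setting was 1,500 trials per scenario, 76 v 68, correlations of 0.7 among pre, post and follow-up, and independent return. The variance of the condition effect with complete cases was 1.55, 1.26 and 1.08 times that of a likelihood model at r = 75%, 85% and 95%. A second setting let 6-month return in the intervention arm rise with the post score (assumed odds ratio 2.7 per SD, base return 75%). A true 0.44 SD effect was then estimated as 0.53 by complete cases and 0.44 to 0.45 by the likelihood model. With no true effect, the complete-case estimate was about +0.09 to +0.10 SD.

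**The case against.** The strongest reply is that a completer analysis and an intention-to-treat analysis are listed as two different things, which would be pointless if they were the same. Values can be filled before a Mancova is run, nothing in the article forbids it, and missing-data detail is commonly left to a fuller protocol or analysis plan that is not shown. This stands. A reader might infer that the intention-to-treat result is bound to be a complete-case result, but the documents do not support that, because it reads a decision into silence.

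A reader might also infer that one missing form or scale removes a parent from everything. That does not follow either. A series of Mancovas is planned, so a missing scale costs only the Mancova that contains it. The 18-month form is outside the 2 × 2 model. A missing pre form matters only if pre scores are covariates.

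On CONSORT tracking, the article says that it makes both analyses possible and does not present it as a method for missing data. That is fair. But tracking only counts losses, and no other route to the intention-to-treat analysis is offered.

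The simulated figures deserve caution too. The return rates, correlations and odds ratio are all assumed. Dependence on the observed post score is the mechanism under which a likelihood model does well. Both methods start from 144 parents, so the simulation says nothing about the loss from 180 to 144.

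What remains is that the article names a specific model beside a specific claim, and that model needs a further step before the claim is true.

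**Conclusion.** The point holds in limited form. As named, the Mancova does not deliver an intention-to-treat comparison on its own, and a better-suited model is available in the same software.

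The firm figures come from the article and depend on one assumption, that pre scores are covariates. This is likely, because the pre wave is left out of the time factor. On that assumption at most 144 of 180 parents enter an unfilled Mancova, and its intervention arm is 97% attenders against 82% as randomised. The result would then lie close to a completer analysis if completers are understood as attenders who returned their forms; the article does not define the term.

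If pre scores are not covariates, the ceiling of 144 falls away, but the requirement for both outcome forms remains. The counts, variance ratios and bias figures for later waves show direction and possible scale only, and the precision gain shrinks as parents who miss one form tend to miss the other.

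**What to change.** In Planned Statistical Analysis, define the intention-to-treat set as all 180 parents in the arm to which they were randomised, and state how those with missing data enter.

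- **Intention-to-treat efficacy analysis:** a likelihood-based linear mixed model (SPSS MIXED) for each scale, with post and 6-month scores as repeated outcomes; condition, time and condition-by-time as factors; and the pre score as covariate. Missing pre scores are multiply imputed using the Family Demographic Survey, which all 180 parents returned before allocation.
- **Acceptable alternative:** multiple imputation followed by the planned Mancova. This keeps the joint test across scales, which separate mixed models give up.
- **Completer or sensitivity analysis:** the unfilled Mancova, labelled as such, with the number entering each arm reported. Name its covariates and say what makes a parent a completer.

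The cost is analysis-section wording and modest analyst time, with no new data; the analyses are described as still to come. The downside is reliance on a missing-at-random assumption. A parent who returned neither outcome form adds no outcome information to the mixed model, so the assumption carries real weight for those parents and should be stated openly.

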This increased recognition of the importance of the transition to adolescence, the potential protective role of parents, and the opportunity to prevent negative outcomes for adolescents [39] has led to the development of a number of parenting programs targeting young adolescents [19,40-43]. Programs for parents of adolescents have typically aimed to improve parenting practices and reduce adolescent risk taking. Early programs were developed for the treatment of distressed families, such as those with adolescents exhibiting antisocial, conduct and delinquent behaviors [39], or to address specific risky behaviors, such as drug misuse [40]. These programs have been demonstrated to result in improvements in child factors such as aggression, conduct disorders and substance misuse [44]. More recently universally targeted adolescent parenting programs have also been developed with the aim of promoting parenting practices that might facilitate prevention or early intervention for serious adolescent mental health, antisocial and delinquent behaviors [45,46].

Despite the increased recognition of the relevance of programs about raising adolescents, research in this area has tended to report lower levels of engagement and higher levels of drop out than programs targeting parents of young children [45-51] with participation rates of parents of older children as low as twenty to twenty-five per cent [52]. Factors that have been identified as impacting on parental enrolment and retention in parenting skill programs include the parents health beliefs (e.g., perceptions of severity of adolescent problems, perceived susceptibility to problems and potential benefits of the program); family socio-economic factors (such as parental education level) and family context (e.g., time demands, scheduling conflicts, timing and frequency of sessions)[53]. Given this, prevention efforts aimed at parents of older children need to incorporate strategies that have been shown to increase parental motivation and actual enrolment in parenting programs. For example, offering programs within close proximity to the family home, with sessions held no more than once per week and preferably on weeknights would address some of the potential contextual barriers to participation[53].

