## Method/Design

### Study Procedures

#### Study Design

This study was a randomised controlled trial in which 180 parents of adolescents were randomly allocated to one of two conditions; intervention or a wait-list control group. Parents in the intervention group participated in the ABCD Parenting Young Adolescents Program, a 6-session behavioral family intervention program which also incorporates acceptance-based strategies [57,59,60]. Those in the wait-list control group did not receive intervention during the 6-month wait list period. Assessments were conducted prior to intervention, immediately after intervention, and 6 months and 18 months after completion of intervention. The wait-list control group completed assessments at the same time as pre, post and 6-month follow-up assessments. The primary outcome measures were improvements in parental psychosocial well being, parenting practices and parent-adolescent relationships. Secondary outcomes included improvements in adolescent behavior and perceived parenting competence. The study was designed to be compliant with the recommendations of the CONSORT statement. [61,62]

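### Efficacy is to be tested in completers and by intention-to-treat with neither named as decisive, and the completer set is formed by different events in the two arms

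*Protocol article*

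**What the plan says.** Under Planned Statistical Analysis, the primary analyses compare the intervention and wait-list conditions at post-intervention and follow-up with mixed Mancovas. The next sentence reads "Both completer and intention-to-treat analyses will be conducted". Neither analysis is ranked above the other, and no rule is given for who counts as a completer.

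Strengths and Limitations presents the pair as an advantage of the design. The tracking of participants is to permit "consideration of engagement processes and a thorough assessment of intervention attrition. This will also allow for both intention-to-treat and completer analyses". The nearness to intervention attrition suggests that completing means completing the program, but the text does not say so.

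On exposure, Study Design states: "Those in the wait-list control group did not receive intervention during the 6-month wait list period".

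On participant flow, the Recruitment section of the Results reports that the 180 parents were "randomly allocated to intervention (n = 90) or wait-list control (n = 90) conditions". Eight of the 90 intervention parents could not be placed in a group, and then "Eight (10%) of the 82 enrolled in a group did not attend".

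Under Assessment Schedule, intervention parents were asked to bring the pre-questionnaire to the first session and were given the post-questionnaire at the last one. Wait-list parents received all questionnaires by mail. The 6-month follow-up was mailed in both arms.

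**The concern.** A completer analysis between randomised arms is a fair comparison only if the same kind of parent is removed from each arm. Here that cannot be arranged. The wait-list has no program to complete during the comparison period, so nobody in it can be excluded for failing to complete. Whatever defines a completer in the intervention arm has no counterpart in the control arm.

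The article itself treats engagement as selective. The Background says "Factors that have been identified as impacting on parental enrolment and retention in parenting skill programs include the parents health beliefs", and goes on to family socio-economic factors and family context. If those characteristics also bear on the outcomes, the difference between completers and controls mixes the effect of the program with the effect of who stays.

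Because the article does not say which analysis decides, a favourable completer result could carry the efficacy conclusion when the intention-to-treat result does not.

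**Working it through.** The plan states no figure of its own on this point, so the check has three parts: the participant flow, the two readings of completer, and an illustration of size.

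**Flow (Results, Recruitment)**
- Intervention: 90 − 8 not placed = 82; 82 − 8 non-attenders = 74. Attendance is 74/90 = 82.2%, and 16/90 = 17.8% received no session.
- Intervention pre-questionnaires: 74 attenders + 2 non-attenders = 76 (84%). All 74 attenders returned one, but only 2 of the 16 non-attenders did.
- Wait-list pre-questionnaires: 68/90 = 76%, so 22 (24%) are missing at baseline.

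The reported counts are internally consistent.

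**Reading 1: completer means program completer.** The intervention arm is cut to at most 74 of 90, and further if a minimum number of sessions is required. The wait-list cannot be cut in this way.

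**Reading 2: completer means questionnaire completer.** At baseline the intervention set is 76 parents, of whom 74 (97%) attended. The post-questionnaire was handed out at the last session, which ties return to attendance again. In the wait-list the set is formed by mail response. Only the 6-month follow-up uses the same route in both arms.

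On both readings the filters act after randomisation and differ by arm.

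**Illustration of size.** Let p = 74/90 be the share attending and D the difference in untreated outcome, in SD, between attenders and non-attenders. D is an assumption; the documents do not give it. The shift of the attender mean from the mean of all randomised is (1 − p) × D = 0.178 × D.

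| Assumed D | Bias (SD) | Share of the planning effect 0.44 (Statistical Power) |
|---|---|---|
| 0.2 | 0.178 × 0.2 = 0.04 | 8% |
| 0.5 | 0.178 × 0.5 = 0.09 | 20% |
| 0.8 | 0.178 × 0.8 = 0.14 | 32% |

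With 74 versus 68 parents, the standard error is √(1/74 + 1/68) = 0.168 SD. If there were no true effect, a two-sided 1% test would then reject in 1.2% to 4.2% of trials for D from 0.2 to 0.8, and a 5% test in 5.5% to 13.5%. This treats the 68 wait-list returners as representative of the 90. Selection among them in the same direction would reduce the net bias, and selection in the opposite direction would increase it.

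**A milder scenario from the article's own data.** Registered and non-registered parents differed on the area socioeconomic index by (1039.6 − 1021.5)/√((68.1² + 74.6²)/2) = 18.1/71.4 = 0.25 SD. Suppose attenders and non-attenders differed by as much, and that the index correlated 0.3 to 0.5 with outcome (assumption). Then D = 0.075 to 0.125, and the bias is 0.178 × D = 0.013 to 0.022 SD, or 3% to 5% of 0.44.

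**Complier effect.** With uptake of 74/90 in the intervention arm and none in the wait-list, the complier average causal effect is the intention-to-treat effect divided by 0.822, which is 1.22 times it. The standard error scales by the same factor.

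**The case against.** The strongest reply is that intention-to-treat is already planned, that the article does not call the two analyses equal, and that defining and ranking analysis sets is often left to a fuller plan. This stands in part. The missing definition is not the defect, and no conclusion has to rest on completers. But the article does commit to a between-arm completer comparison within its primary efficacy analyses, and the difficulty arises under either definition.

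A reader might infer more than the documents support:
- **That the analysis selects parents on the number of sessions received.** No session threshold is given. Program completion is suggested by the context but not stated.
- **That the control arm is unselected.** It is not: 22 of its 90 parents returned no pre-questionnaire, against 14 of 90 in the intervention arm. The arms are differently selected.
- **That all 16 parents without a session opted out.** Eight of them could not be placed in a group, and no reason is given.
- **That the bias must favour the program.** Perceived severity is among the engagement factors in the Background, and some families did not register because the problem had resolved. Parents who stay could have the harder cases.
- **That the socioeconomic difference measures the bias.** It arose at registration, before allocation, so it cannot unbalance the arms. It only shows that selection of this kind occurs. The plan also intends to explore socioeconomic status as a confounder.

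A complier analysis can also be challenged because few non-attenders supplied data. That is a real limit, but it applies equally to the intention-to-treat analysis already planned.

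**Conclusion.** The concern holds as a point about how the completer comparison is formed and where it ranks. Randomisation does not protect that contrast, and the article does not say that intention-to-treat takes precedence over it.

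The direction and size of the bias cannot be derived from the documents. The range of 0.04 to 0.14 SD rests on the assumed D of 0.2 to 0.8, on attendance at any session as the completer rule, and on wait-list returners being representative. The socioeconomic scenario alone gives only 0.01 to 0.02 SD. A stricter completer rule would exclude more parents and so widen the range for the same D. The point is worth correcting because the remedy is nearly free, not because a large distortion has been shown.

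**What to change.** 1. State that the intention-to-treat contrast of all 90 versus 90 decides efficacy.
2. If a between-arm completer comparison is kept, define completer for each arm and label the comparison supportive only.
3. To estimate the effect in parents who received the program, prefer a complier average causal effect. Use random allocation as the instrument and attendance at one session or more as receipt. A stricter threshold would assume that partial attendance has no effect. The method also assumes that allocation alone does not change outcomes in parents who never attend. It further needs no wait-list uptake before follow-up; the article says wait-list parents generally completed follow-up before starting the program, so any exceptions should be checked.
4. Present results by number of sessions descriptively, within the intervention arm.

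**Cost.** Items 1 and 2 are wording, and item 3 is one further model. The interval will be wider than the intention-to-treat interval by the factor 1.22. The complier analysis needs the same missing-data assumptions for non-attenders as intention-to-treat. These are substantial, since only 2 of the 16 returned a pre-questionnaire, and they should be stated openly.
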